In 2013, the Philippines, considered an LMIC, had an overall diabetes prevalence of 6.0%, an estimated 1.7 million people with undiagnosed diabetes, and 54,535 diabetes-related deaths [6]. The Philippines is estimated to have over 6 million people with diabetes by the year 2035 [1]. The Philippines has begun implementation of the World Health Organization Package of Essential Noncommunicable Disease Interventions for primary care settings in low resource areas [7], created the National Centre for Disease Prevention and Control in 2000 including a diabetes-specific office, and has listed reduction of mortality and morbidity from lifestyle-related diseases such as diabetes as one of the goals in the “National Objectives for Health 2005-2010” [8]. However, there are currently some gaps in the areas of detection and treatment for diabetes. For example, though screening kits and medications are available at no cost, the case detection for new cases of diabetes is poor, the diabetes registry is poorly maintained, and the medications often get left unused in the stockrooms of local health centres ([name], Philippine Department of Health, personal communication, June 16, 2014). Knowledge about diabetes is also a gap in the Philippines; in a study in one region of the Philippines the mean score for diabetes knowledge among people diagnosed with diabetes was only 43% [9].

The Cardiovascular Health Awareness Program (CHAP) intervention model may be particularly suited to LMICs due to its low cost, implementability, and focus on population-based health promotion and disease prevention. CHAP is a community-based, primary care-centred, volunteer-led, free of charge, cardiovascular disease risk assessment and blood pressure monitoring program, which is combined with health education sessions for community-dwelling older adults [10]. A large community cluster randomized controlled trial in Canada demonstrated that the CHAP intervention resulted in a statistically significant 9% reduction in annual hospital admissions due to stroke, heart failure, and heart attacks in people aged 65 and over at the population [11]. The CHAP has been successfully expanded to include a diabetes risk assessment component in the Community Health Awareness of Diabetes (CHAD) program and other community adaptations [12, 13].

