#### Secondary outcomes and measures

There are a number of secondary outcomes which will evaluate the mean differences between intervention and control groups at 6 months. These outcomes, whether they pertain to cluster or individual participant level, and their measures and sources are listed in Table 1.

**Table 1 Tab1:** Secondary Outcomes

Outcome	Level	Measure, Source
Physical activity	Individual	International Physical Activity Questionnaire (IPAQ) [22] and modified CP@clinic survey [13]
Medication compliance	Individual	Survey questions (self-reported)
Blood pressure	Individual	Physical measurements
Risk factors for diabetes	Individual	Finnish Diabetes Risk Score (FINDRISC) [23] on community survey
Risk behaviours for diabetes / cardiovascular issues (activity, diet, smoking, alcohol, stress)	Individual	Elements of the Health Awareness and Behaviour Tool (HABiT) on community survey (self-reported)
Knowledge about diabetes and hypertension	Individual	Elements of the HABiT on community survey (self-reported)
Perceived concern and understanding of risk	Individual	Elements of the HABiT on community survey (self-reported)
Confidence in behaviour change	Individual	Elements of the HABiT on community survey (self-reported)
Number of community residents newly diagnosed with diabetes	Cluster	Rural Health Unit databases
^a^Hospital admission rates due to diabetes and diabetes-related conditions, hypertension, myocardial infarction (MI), stroke, congestive heart failure	Cluster	Central Department of Health database
^a^Mortality rates due to diabetes and diabetes-related conditions, hypertension, MI, stroke, congestive heart failure based on ICD-10 codes	Cluster	Regional Field Health Surveillance Information Systems

^a^Hospital admission rates and mortality rates will be measured for both the 12 months before and the 12 months after the CHAP-P implementation, and will be divided by the mid-year population estimates

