**Fig. 3 Fig3:**
[figure not shown]
CHAP-P Intervention

Based on findings during the assessment, BHWs will educate the CHAP-P participants on diabetes, cardiovascular risk factors, and healthy lifestyles, providing educational materials that have been adapted for a local context (including materials such as pamphlets, comic strips, and videos). Those CHAP-P participants whose FINDRISC scores indicate diabetes risk (moderate: score of 12–14, high: score of 15–20, or very high: score of > 20) will be referred to the Rural Health Unit for fasting blood glucose testing. Those who have blood pressure greater than 140/80 mmHg will be referred to the midwife, with those with blood pressure over 180/100 mmHg being immediately referred to the Rural Health Unit or District Hospital, and those with blood pressure under 180/100 mmHg being referred to the Rural Health Unit with less immediacy, for further evaluation and management. Those with other specific risk factors such as low physical activity, high salt intake, or smoking will be given further health education and referred to appropriate local programs. CHAP-P sessions will continue to be held twice a month in intervention communities, and residents will be encouraged to continue attending for ongoing follow-up and monitoring. The monthly observational fidelity checklists from research assistants will be undertaken to improve adherence to intervention protocols.

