3. What is the difference in diabetes-specific outcomes between communities implementing CHAP-P and those not implementing CHAP-P?: (a) screening rates for diabetes, (i.e., rates of newly diagnosed cases of type 2 diabetes), (b) initiating medication treatment for diabetes management, and (c) hospital admission rates and mortality due to diabetes (and its complications), hypertension, myocardial infarction, stroke, and congestive heart failure? (d) self-reported health utilization and access	• a. N community residents newly diagnosed with diabetes (Rural Health Unit databases) • b. N community residents newly initiating medication treatment • c. Hospital admission rates due to diabetes and diabetes-related conditions, hypertension, MI, stroke, CHF (central Department of Health database) • d. Mortality rates due to diabetes and diabetes-related conditions, hypertension, MI, stroke, CHF based on ICD-10 codes (Regional Field Health Surveillance Information Systems) • e. Availability of health care services in community and whether there is a place they go when sick or need health advice (2 items; self-report)	a., b., c., d. N/A – administrative records representing intervention and control communities e. Community survey participants	a., b. T_6_ (for 6 months of program) c., d. T_−12_, T_12_ (for 12 months before & after program, divided by mid-year population estimates) e. T_0_, T_6_	Intervention over control communities will have more residents newly diagnosed with diabetes, more residents newly initiating medication treatment for diabetes, a lower hospital admission rate due to diabetes and related conditions, and a lower mortality rate due to diabetes and related conditions	Generalized estimating equations (linear and Poisson Model, adjust for clustering effect)
4. What is the cost-effectiveness and cost-utility of CHAP-P compared to usual care?	• Program cost (actual) • Healthcare resource utilization costs (self-report, survey) • Percentage reduction in HbA1c (A1C Now+ point-of-care device) • Quality of life (EQ-5D-5 L) • Quality-Adjusted Life Years (QALYs) (calculated from EQ-5D-5 L)	Community survey participants (healthcare resource utilization, HbA1c, quality-of-life)	T_0_, T_6_	Not appropriate for this type of outcome	*Cost-effectiveness:* percentage decrease in HbA1c *Cost-utility:* cost per QALY (based on local EQ-5D-5 L)

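### Admissions and deaths coded to diabetes or hypertension are hypothesised to fall, yet case-finding added only in the intervention arm can raise those codes without any change in health

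*Protocol article*

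**What the plan says.** Table 1 (Secondary outcomes and measures) and Table 2, Research Question 3 (Quantitative outcomes) define two cluster-level, cause-specific outcomes from routine records.

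- Admissions, as worded in Table 2: "Hospital admission rates due to diabetes and diabetes-related conditions, hypertension, MI, stroke, CHF (central Department of Health database".
- Deaths, as worded in Table 1: "Mortality rates due to diabetes and diabetes-related conditions, hypertension, MI, stroke, congestive heart failure based on ICD-10 codes".

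Both are measured over the 12 months before and the 12 months after implementation, divided by mid-year population, and analysed with generalized estimating equations (GEE).

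The hypothesis cell for Research Question 3 makes two predictions. The first is "Intervention over control communities will have more residents newly diagnosed with diabetes, more residents newly initiating medication treatment for diabetes". The second is "a lower hospital admission rate due to diabetes and related conditions, and a lower mortality rate due to diabetes and related conditions".

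The Intervention section describes what only intervention communities receive. Session attendees with a raised diabetes risk score "will be referred to the Rural Health Unit for fasting blood glucose testing". Raised blood pressure also leads to referral, "with those with blood pressure over 180/100 mmHg being immediately referred to the Rural Health Unit or District Hospital".

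The Background says that case detection in the Philippines is poor and the diabetes registry badly kept.

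**The concern.** Routine records attribute an admission or death to diabetes or hypertension more readily when the condition is already known. The intervention is built to make it known more often, and in one arm only. Allocation can therefore change how these outcomes are ascertained as well as how often they occur, and the ascertainment effect works against the program.

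What is at stake is interpretation. If the rate of diabetes- or hypertension-coded events is unchanged or higher in intervention communities, the reader cannot tell a program that failed from one that succeeded in finding cases. The Discussion says the results will be shared with policymakers. The article describes no check that is independent of coding.

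**Working it through.** The article gives no event rate, cause mix, effect size or power for admissions or mortality, so there is no stated figure to reproduce. The check has three steps.

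**1. Does the design remove the problem?**

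- Randomization does not, because the coding shift would follow from allocation.
- The 12-month pre-period does not. It captures baseline differences, whereas this shift begins with the program.
- GEE does not. It handles correlation within communities, not differential measurement.
- Recoding between listed causes cancels in a pooled total. The exposure lies in the diabetes- and hypertension-specific rates, and in a pooled total only to the extent that events move in from unlisted causes or are newly generated by referral.

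**2. How large a coding shift would matter?**

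Let RR be the true rate ratio, s the share of counted events coded to diabetes or hypertension, and f the relative rise in such events due to coding or referral in the intervention arm.

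- Observed rate ratio = RR × (1 + s × f)
- Shift that cancels the benefit: f = (1/RR − 1)/s

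Assumptions: RR = 0.91, taken from the parent program's "statistically significant 9% reduction in annual hospital admissions due to stroke, heart failure, and heart attacks" (Background) as a benchmark of size only; s and f are assumed over a range. Here 1/0.91 − 1 = 0.0989.

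| s | Observed ratio, f = 10% | Observed ratio, f = 20% | f that cancels the benefit |
|---|---|---|---|
| 20% | 0.928 | 0.946 | 0.0989/0.2 = 49% |
| 40% | 0.946 | 0.983 | 0.0989/0.4 = 25% |
| 60% | 0.965 | 1.019 | 0.0989/0.6 = 16% |
| 100% | 1.001 | 1.092 | 0.0989/1.0 = 10% |

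The last row is a rate made up only of diabetes- and hypertension-coded events. With RR = 0.80, 1/0.80 − 1 = 0.25 and the cancelling shifts are 125%, 63%, 42% and 25%.

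**3. What rise in diagnosis would produce such a shift?**

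Assumption: the global undiagnosed share of 45.8% (Background) holds locally, so 54.2% are diagnosed. This covers diabetes only.

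| Diagnosed share after | Share of undiagnosed newly found | Inflation if only known cases are coded | Inflation if half of the unknown cases are recognised in hospital |
|---|---|---|---|
| 60% | 5.8/45.8 = 13% | 60/54.2 = 1.107 | (60 + 20)/(54.2 + 22.9) = 1.038 |
| 65% | 10.8/45.8 = 24% | 65/54.2 = 1.199 | (65 + 17.5)/(54.2 + 22.9) = 1.070 |
| 70% | 15.8/45.8 = 34% | 70/54.2 = 1.292 | (70 + 15)/(54.2 + 22.9) = 1.102 |

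For a diabetes-only rate, a 10% inflation thus needs a diagnosed share of about 60% with no recognition in hospital, or about 70% with half recognised. In a pooled rate the inflation is multiplied by s: at s = 20% to 40%, 3.8% becomes 0.8% to 1.5%.

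**The case against.** The strongest replies, and what stands of each:

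- **The outcomes are events due to the condition, and hospitals can diagnose during the admission.** This stands. A reader might infer that an event can be coded to diabetes only if it was known beforehand. The article does not say how causes are coded and does not support that reading. Recognition at admission shrinks the effect; it removes it only if recognition is complete.
- **Community reach may be too low.** This largely stands. Finding 13% to 34% of all undiagnosed residents, net of control, is a lot in barangays of 3000 to 20,000 people with sessions twice a month. The Discussion admits that recruitment to sessions can be difficult. Nothing in the article supports a particular shift.
- **The 9% is for other events.** This stands. It refers to stroke, heart failure and heart attack, so a reader should not conclude that the coding artefact is as large as the expected benefit and opposite in sign.
- **The two hypotheses are compatible.** This stands. More detection, then treatment, then fewer events is the intended chain, and referral for evaluation is not an admission. The problem is that the outcome cannot separate that chain from a change in labelling, not that the cell contradicts itself.
- **If causes are analysed separately, the robust rates are already available.** This stands in part. The article leaves pooled or separate analysis open, as an article may. The single hypothesis of a lower rate still covers the diabetes-coded events.

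**Conclusion.** The point holds as a problem of differential ascertainment in the diabetes- and hypertension-coded parts of two secondary outcomes. The direction, against the intervention, follows from what the article states: case-finding in one arm, a predicted rise in diagnosis, and cause-specific outcomes from routine records. The size does not follow. The figures above rest on an assumed cause mix, an assumed coding shift and a global undiagnosed share applied locally, and the true effect may be small.

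A reader might infer that secondary aim iii as a whole becomes unreadable. The documents do not support that. Its screening and treatment-initiation parts are untouched, MI, stroke and CHF codes depend much less on prior diagnosis, and the primary HbA1c comparison is unaffected. What cannot be read alone is a null or raised rate of diabetes- or hypertension-coded admissions or deaths.

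**What to change.** Keep the listed outcomes and make three changes to Tables 1 and 2 and the accompanying text:

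1. Analyse MI, stroke and CHF separately from diabetes- and hypertension-coded events, for both admissions and deaths.
2. Add all-cause admission and all-cause mortality rates from the same databases, if these hold all-cause counts, as coding-independent checks.
3. State that the diabetes- and hypertension-coded rates are subject to differential ascertainment, and are not to be taken alone as evidence of benefit or harm.

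The cost is some rewording and a few more analyses. All-cause rates are diluted by unrelated events, so they serve as a check and not as a sensitive test.

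Do not make MI, stroke and CHF the only tested outcome. If attribution moves from MI or stroke to newly known diabetes, those events leave the count and the program looks better than it is, which replaces a bias against the intervention with one in its favour.

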#### Qualitative analysis

Transcripts will be cleaned and data will be summarized using thematic analysis (open coding axial coding, selective coding). QSR International NVivo 11 qualitative analysis software [32], will be used to store and manage qualitative data.

#### Economic analysis

Percentage decrease in participant HbA1c will be the measure of effectiveness used in the cost-effectiveness analysis. Cost per QALY will be calculated as the cost-utility measure; QALYs will be computed based on local EQ-5D-5 L values. Both cost-effectiveness and cost-utility analyses will include overall program cost measures and participant health resource utilization and cost thereof.

#### Power and sample size

CHAP-P is a community-wide intervention and community sizes vary from 3000 to 20,000 residents. We are using paired randomization, therefore intervention and control community pairs need to have relatively similar sizes. Our sample size for individuals was calculated based on a mean difference of HBA1c of 0.2% (SD = 1.09) with standard parameters (alpha = 0.05, power = 0.80). This required a sample size of 520 per arm. Based on our pilot, the intraclass correlation coefficient (ICC) was 0.006. We increased our ICC to 0.01 which inflated our sample size to 1034 per arm. We have opted to take 26 (13 pairs of intervention: control) communities with 100 residents per community giving a total sample size of 2600 residents (1300 per arm).

## Discussion

This study will provide a robust evaluation of a community diabetes program in the Philippines. Though the country is committed to preventing and treating lifestyle-related diseases such as diabetes, the level of commitment to implement programs and the amount of diabetes-related activities already being implemented varies greatly among communities [8]. Some community-based programs for type 2 diabetes tested in other LMICs including elements such as educational sessions, lifestyle instruction, and self-monitoring have shown significant positive outcomes including lowering weight, waist circumference, fasting plasma glucose levels, and HbA1c [33, 34]. Diabetes self-management programs and other community-based interventions are being implemented across the Philippines, yet large-scale experimental studies are still a gap in the literature [9, 35–37]. This study will help fill that gap.

A major strength of this study is the multi-phase, multi-year nature of the overall research program. The intervention was based on the evidence-based CHAP model from Canada, though needed to be adapted for the local context. Phase 1, the qualitative community scan, and Phase 2, piloting the elements, were vital to integrate the components and building a diabetes intervention that would make sense in the context of the Zamboanga Peninsula, Philippines. The mixed methods design included throughout the research program is another strength, with qualitative data included in this RCT to help explain and interpret quantitative results. Initially, a stepped-wedge cluster RCT was planned rather than a parallel cluster RCT, yet instead of solving issues of logistical constraints [38], it introduced some - the stepped-wedge design would have been more expensive and more time-consuming. Due to the variation in communities across the Philippines, the focus on a community-level approach is a key element in making a program such as CHAP-P work. The integration of perspectives from multiple key stakeholders throughout the process solidifies communities’ buy-in to the project. Finally, the health economics component of this study will provide policymakers and funders the information they need to decide whether implementation of a program such as CHAP-P is cost-effective for their communities.

Though we combined many elements to fit the program to the setting, there are still some limitations that warrant consideration. First, recruitment for CHAP-P sessions can be difficult, particularly within urban areas, and as a community intervention it is important to reach a substantial portion of the community. To improve penetration within the communities, we have decided to ensure the CHAP-P sessions rotate between *puroks* (a subdivision of a barangay) rather than having them in the same location week-by-week. Second, the mobile HbA1c test kit can be difficult to work with, as it only lasts for approximately 5 minutes in the heat and humidity of the Philippines. Due to that constraint, all HbA1c tests are now completed at a common community location; however, those locations still need refrigeration for the test kits, so access to refrigerated space is an inclusion criterion for communities. Finally, during the pilot studies there were some security concerns in the region that limited travel of the research team, so something similar may occur during the RCT implementation. This may affect the ability of the research team to visit communities for monthly fidelity checks, yet the intervention will be able to continue as BHWs can continue facilitating CHAP-P sessions in their local communities.

This study has the potential to improve diabetes detection, management, and prevention in the Philippines and similar LMICs. The results from this study will be shared with policymakers (municipal, provincial, regional, national) in the Philippines and our research partners in other LMICs and the Global Alliance for Chronic Diseases. Results will also be published in relevant conference and journals to disseminate our findings to other researchers and policy makers planning to implement an out-of-the-box program for diabetes detection, management, and prevention.

## Abbreviations

ADZU: Ateneo de Zamboanga University, Philippines
BHW: Barangay Health Worker
CHAD: Community Health Awareness of Diabetes
CHAP: Cardiovascular Health Awareness Program
CHAP-P: Community Health Assessment Program in the Philippines
CIHR: Canadian Institutes of Health Research
EQ-5D-5 L: EuroQol-5 dimension-5 level (quality of life measure)
FINDRISC: Finnish Diabetes Risk Score (measure)
GACD: Global Alliance of Chronic Diseases
HABiT: Health Awareness and Behaviour Tool
HbA1c/A1C: Glycated hemoglobin
HiREB: Hamilton Integrated Research Ethics Board, Canada
IDRC: International Development Research Centre
IPAQ: International Physical Activity Questionnaire (measure)
LMIC: Low- to middle-income country
QALY: Quality-adjusted life year
RCT: Randomized controlled trial
